### Methods

#### Data sources

CPRD is a database of primary care electronic health record data (available online via CPRD GOLD) from participating general practices, covering 7% of the UK population.^18^ Patients included in CPRD are largely representative of the UK population in terms of age, sex, ethnicity and body mass index. HES covers all hospital admissions for all English patients whose treatment is funded by the UK National Health Service (NHS), whether treated by the NHS or by independent providers.^19^ Seventy-five per cent of English general practices included in CPRD are linked to HES data.^18^ We obtained data from 1 April 2009 to 31 July 2017; this period covers the introduction of the newer antiplatelet agents prasugrel and ticagrelor. This study protocol has been approved.

### Study populations

Eligibility and exclusion criteria for the three target trials (for patients undergoing PCI, patients undergoing CABG or patients hospitalised and conservatively managed for ACS) are listed in table 1. We will identify eligible patients who are included in Clinical Practice Research Datalink (CPRD) and eligible for linkage with Hospital Episode Statistics (HES) and Office for National Statistics (ONS) mortality data (because they have a valid NHS number and are registered at a practice that was participating in the linkage programme). Patients are included if they had a PCI, CABG or ACS (index event) record in HES during the study period (1 April 2010–31 January 2017), and have at least 1 year of linked CPRD-HES data before the date of their index event. They must also have been prescribed one of the treatment regimens being compared in the target trial corresponding to their index event. One year’s data preceding eligibility for the target trial is adequate to apply most of the exclusion criteria and determine comorbidities and medication history: such information would be collected at baseline in a randomised trial. The following Office of Population Censuses and Surveys (OPCS) procedure codes (PCI and CABG) and International Classification of Diseases (ICD-10) codes (ACS no procedure) will be used to identify patients: PCI, K49, K50 & K75; CABG, K40, K41, K42, K43, K44, K45 & K46; ACS without a procedure, I20.0, I21, I22, I24.9 (with no OPCS code for PCI or CABG in the same hospital admission). Figure 1 shows full details of the inclusion and exclusion criteria.

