Eligibility criteria	Target trial 1 (PCI) Consecutive patients (age ≥18 years) undergoing PCI (emergency or elective). Exclusions: DAPT or anticoagulant use in the previous 3 months; major bleed requiring hospitalisation in previous 12 months; renal failure requiring dialysis; intolerance/allergy to aspirin, clopidogrel, prasugrel or ticagrelor. Target trial 2 (CABG) Consecutive patients (age ≥18 years) undergoing CABG (urgent and elective). Exclusions: DAPT or anticoagulant use in the previous 3 months; other concomitant cardiac surgery (eg, valve surgery); major bleed requiring hospitalisation in previous 12 months; renal failure requiring dialysis; intolerance/allergy to aspirin, clopidogrel, prasugrel or ticagrelor. Target trial 3 (conservatively managed ACS) Consecutive patients (age ≥18 years) hospitalised for an acute coronary syndrome (ACS): myocardial infarction (MI) with or without ST elevation or unstable angina. Exclusions: PCI or CABG performed at time of ACS diagnosis; major bleed requiring hospitalisation in previous 12 months; renal failure requiring dialysis; intolerance/allergy to aspirin, clopidogrel, prasugrel or ticagrelor.	CPRD-HES linked data set contains information that allows us to identify all eligible patients for the three target trials. The study period is April 2009–July 2017. All eligible patients will have sufficient data (1 year) preceding their index event to apply the exclusion criteria and characterise the population (eg, comorbidities) and sufficient follow-up data (1 year) to identify outcomes. It is not possible to capture intolerance/allergy to aspirin, clopidogrel, prasugrel or ticagrelor.
Interventions	Target trial 1 (PCI) Clopidogrel (75 mg daily) or prasugrel (5 mg or 10 mg daily) or ticagrelor (90 mg twice daily). All patients will receive aspirin (at a dose of 75 mg daily, in line with current guidelines). Target trial 2 (CABG) Clopidogrel (75 mg) in addition to aspirin (at a dose of 75 mg daily, in line with current guidelines) or aspirin only (any dose, reflecting variation in usual care). Target trial 3 (conservatively managed ACS) As for target trial 2.	Relevant interventions can be identified as CPRD has information on all medications (including doses) prescribed in primary care.

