Assignment to interventions	Participants are assigned to DAPT interventions in hospital.	Participants enter the study at index procedure date for PCI and CABG, and episode start date for ACS, and will be assigned to DAPT interventions using first prescription in CPRD (within 2 months of hospitalisation) as a proxy for what they were prescribed in hospital (there are no medications data in HES). This assignment will exclude a proportion of eligible patients (those who died or experienced a major bleed that caused them to stop DAPT, or patients who have no prescription for DAPT within the 2-month window); we will identify and describe the characteristics of these excluded patients. In sensitivity analyses, we will address the robustness of results to different assumptions about the intervention group in those patients where the DAPT medication is unknown or a major bleed occurs prior to the first DAPT medication, by using multiple imputation models for handling missing data. Prior known information regarding the likely prescription based on patient characteristics or general policies will be incorporated in these analyses.
Follow-up	Starts at assignment to intervention and ends at first bleed or 12 months from assignment (whichever comes first).	Starts at time of hospitalisation for PCI, CABG or ACS and ends at first bleed or 12 months from hospitalisation (whichever comes first).
Primary outcome	Any bleed within 12 months of the start of DAPT (DAPT is prescribed at hospitalisation for PCI, CABG or ACS).	Any bleed within 12 months of hospitalisation for PCI, CABG or ACS.
Analysis	Intention to treat	According to first prescription for DAPT in CPRD

CABG, coronary artery bypass grafting; CRPD, Clinical Practice Research Datalink; DAPT, dual antiplatelet therapy; HES, Hospital Episode Statistics; PCI, percutaneous coronary intervention; PICO, Population, intervention, comparator, outcome.

In patients who have undergone PCI, estimate the effect on bleeding events of assignment to aspirin and clopidogrel (reference) versus aspirin and prasugrel or aspirin and ticagrelor.In patients who have undergone CABG, estimate the effect on bleeding events of assignment to aspirin (reference) versus aspirin and clopidogrel.In patients who are conservatively managed after presenting with ACS, estimate the effect on bleeding events of assignment to aspirin (reference) versus aspirin and clopidogrel.

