### Follow-up

The start of follow-up (the index event) will be the date of the index hospital procedure (PCI, CABG) or start date of the hospital episode that contains the ACS diagnosis (ACS). Patients will be followed up until 12 months after the index event, since DAPT is prescribed for 12 months in accordance to guidelines.

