### Statistical analyses

We will describe temporal changes in DAPT prescribing and bleeding for PCI, CABG and ACS populations. We will use descriptive statistics to summarise the characteristics of the different intervention groups and standardised mean differences to compare them. We will estimate rates of bleeding (number of events/person time) with 95% CIs for each group. We will separate major and minor bleeding since adverse events of each type have different health and resource use consequences.

Analyses will estimate the effects of assigned intervention (analogous to an intention-to-treat analysis of a randomised trial) for the antiplatelet regimens corresponding to the first prescription of aspirin or DAPT in CPRD (see Interventions). We will use parametric survival models to estimate adjusted HRs with 95% CIs for the time to first bleeding event, comparing intervention groups for each target trial. Exploratory analyses, including assessment of proportional hazards assumptions, will be used to inform the choice of survival distribution (eg, Weibull). Estimated time-dependent event probabilities will be used to update existing cost-effectiveness models.^26^ The confounding factors to be included in the model (which will be identified as described previously and grouped into confounding domains from our data set), the modelling strategy and the approach to handling correlated covariates will be documented in a data analysis plan. Participants free from a bleeding event will be censored at 12 months after the index event. For secondary endpoints, we will use survival models to estimate adjusted HRs with 95% CIs for time to first event. For mortality outcomes, we will take account of the competing risks of death due to other causes.

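### Index events run to 31 January 2017 but the data end on 31 July 2017, so Table 1's 1-year follow-up statement and the 12-month censoring rule fail for the last six months of index events

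*Protocol article*

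**What the plan says.** All places are in the protocol article.

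- **Data sources** gives the extract: "We obtained data from 1 April 2009 to 31 July 2017".
- **Study populations** gives the index window, a PCI, CABG or ACS "record in HES during the study period (1 April 2010–31 January 2017". It requires patients to "have at least 1 year of linked CPRD-HES data before the date of their index event". It sets no matching requirement after the index event.
- **Table 1, Eligibility criteria row** says "The study period is April 2009–July 2017" and then that all eligible patients will have, besides the year of prior data, "sufficient follow-up data (1 year) to identify outcomes".
- **Table 1, Follow-up row** says that follow-up in the emulation "ends at first bleed or 12 months from hospitalisation (whichever comes first".
- **Follow-up** says "Patients will be followed up until 12 months after the index event".
- **Statistical analyses** says "Participants free from a bleeding event will be censored at 12 months after the index event".

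None of these places names the end of the data as an end of follow-up.

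**The concern.** The index window opens one year after the extract begins, which is exactly what the look-back requires. At the other end it closes only six months before the extract does, although the outcome window is 12 months. The statement about one year of follow-up therefore cannot be true for the latest patients.

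The same gap reaches the primary analysis. If a patient indexed in late 2016 has no recorded bleed by 31 July 2017 and is censored at 12 months as written, the months after July 2017 enter the analysis as observed bleed-free time. Bleeding rates per person-time, the survival-model HRs and the time-dependent event probabilities meant for the cost-effectiveness models would all use that time.

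**Working it through.** **Inputs.** Extract 1 April 2009 to 31 July 2017 (Data sources). Index window 1 April 2010 to 31 January 2017 (Study populations). Follow-up 12 months (Table 1, Follow-up, Statistical analyses). Uniform accrual over the index window is an assumption, because no counts by year are given.

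**1. Look-back.** 1 April 2009 to 1 April 2010 is 365 days, so the stated year of prior data is attainable for the first patient.

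**2. Follow-up.** Available follow-up = 31 July 2017 minus index date.
- Index on 31 January 2017: 181 days.
- Index on 1 August 2016: 364 days, the first date that falls short of 365.
- The stated 1 year for all eligible patients is therefore not reproduced.

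**3. Share affected.** 1 August 2016 to 31 January 2017 is 184 days, and the whole window is 2498 days: 184 / 2498 = 7.4%.

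**4. Person-time.** The shortfall runs from 1 to 184 days, with mean (1 + 184) / 2 = 92.5 days.
- As a share of credited time: 0.0737 × 92.5 / 365 = 1.87%.
- Relative to observed time: 0.0187 / (1 − 0.0187) = 1.9%.
- This treats every patient as credited with the full year and ignores the minority whose follow-up ends earlier at a bleed.

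**5. An arm used mainly late in the window (assumption).** Suppose an arm accrued uniformly over only the last 5 or the last 3 years of the window.
- 5 years: 184 / 1826 = 10% of patients; 0.101 × 92.5 / 365 = 2.6% of credited time, and 2.6% relative to observed time.
- 3 years: 184 / 1096 = 17% of patients; 0.168 × 92.5 / 365 = 4.3% of credited time, or 4.4% relative to observed time.

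**6. Effect on an HR (constant hazard assumed).** If the reference arm is overstated by 1.9%, the HR is multiplied by 1.019 / 1.026 = 0.99 to 1.019 / 1.044 = 0.98. If the reference arm had no overstatement at all, the most extreme factor is 1 / 1.044 = 0.96. For scale, the unadjusted PCI HR detectable with 90% power in Table 2 is 1.48.

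**7. Effect on power.** HR = exp[(1.960 + 1.282) / √(E·p·(1 − p))], with E = 700, 180 and 680 events and p = 1/9, 1/5 and 1/3.5 for PCI, CABG and ACS. The first row reproduces Table 2 to within rounding. The other rows apply the loss to the stated event counts.

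| Unadjusted HR, 90% power | PCI | CABG | ACS |
|---|---|---|---|
| Stated events (Table 2: 1.48, 1.83, 1.32) | 1.48 | 1.83 | 1.32 |
| Window kept, censored at end of data (1.87% fewer events) | 1.48 | 1.84 | 1.32 |
| Window ended 31 July 2016 (7.4% fewer events) | 1.50 | 1.87 | 1.33 |

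**The case against.** The strongest reply is that no competent analyst credits time beyond the end of the extract. The article leaves the modelling strategy to a data analysis plan that is not shown, and administrative censoring is the kind of detail a condensed article leaves there. This stands in part: the harm is conditional on a literal reading, and rules on matters such as transfer out of a practice or the end of linkage can sit in that plan. It does not remove the point. The article is not silent. It makes a statement about follow-up that its own dates rule out, and it fixes an end of follow-up in three places, each without the end of data. Figure 1 is not available here, but it could not supply data after July 2017.

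A reader might infer three stronger things that the document does not support.

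- **That prasugrel and ticagrelor will be made to look safer.** Data sources says the period spans the introduction of these agents, so late concentration is plausible, but no counts by year are given. It would touch only the PCI comparison, because the CABG and ACS comparisons set aspirin alone against aspirin with clopidogrel. The sensitivity-analysis text also expects most bleeds soon after the index event, so few may fall in the unobserved months.
- **That a year of follow-up is an entry condition, so that patients are selected on their future.** The eligibility text requires only prior data, and all-cause mortality is a secondary outcome, which fits badly with requiring a year of survival.
- **That the two definitions of the study period conflict in substance.** One is the extract and the other the index window. Using one label for both is editorial.

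**Conclusion.** The contradiction is certain, since it follows from the stated dates alone. Index events from 1 August 2016 cannot have the year of follow-up that Table 1 gives to all eligible patients, and the 12-month censoring rule is wrong for those who stay bleed-free.

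The consequence is modest. About 7.4% of index events are affected, and person-time would be overstated by about 1.9% if the rule were applied literally; both figures assume uniform accrual. An overstatement of 2.6% to 4.4% in the newer-agent PCI arms rests on the further assumption that their use was confined to the last 3 to 5 years of the window. Even then the HR would shift by only about 1% to 2%, or about 4% in the extreme case of no overstatement in the reference arm.

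The reason to act is that a stated fact and a primary-outcome rule are wrong and almost free to correct. No large bias has been shown.

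**What to change.** 1. In Table 1 (Eligibility criteria row), remove the statement that all eligible patients have one year of follow-up data. Say instead that patients indexed after 31 July 2016 have between about 6 and 12 months.
2. In Table 1 (Follow-up row), Follow-up and Statistical analyses, state one rule: follow-up ends at the earliest of first bleed, 12 months after the index event, death, and the end of the patient's available linked data, 31 July 2017 at the latest.
3. As an editorial tidy-up, use different labels for the extract and the index window.

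This costs wording only. No patients are lost, and the detectable HRs move by at most about 0.01 in the unadjusted 90%-power rows.

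Ending the index window on 31 July 2016 would also make the Table 1 dates consistent. It gives up about 7.4% of index events, and on the late-uptake assumption 10% to 17% of the prasugrel and ticagrelor arms, which are the smallest PCI groups (842 and 770 patients). It is not needed, because survival models handle the shorter follow-up once censoring is stated correctly.

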### Interventions

The interventions of interest for the three target trials are shown in table 1. Guidelines recommend low dose aspirin (75 to 100 mg/d) plus either clopidogrel (75 mg/d), prasugrel (5 mg/d or 10 mg/d) or ticagrelor (90 mg twice/d) for PCI and conservatively managed patients with ACS. For PCI patients, the interventions of interest are aspirin and clopidogrel, aspirin and prasugrel and aspirin and ticagrelor. In conservatively managed patients with ACS, clopidogrel is the most commonly prescribed second antiplatelet agent (in addition to aspirin) and a large proportion of patients are prescribed aspirin only; therefore, the interventions of interest are aspirin only (75 to 100 mg/day) and aspirin and clopidogrel. There is variation in aspirin prescription for CABG patients; some surgeons choose 75 mg/day, others 150 mg/day or 300 mg/day. Surgeons may also prescribe an additional antiplatelet agent, most commonly clopidogrel. Therefore, the comparisons of interest in CABG patients are aspirin only (any dose, reflecting variations in usual care in different hospitals) and aspirin and clopidogrel (doses as for PCI). We have specified these comparisons based on preliminary feasibility counts from CPRD, which indicate that few CABG and conservatively managed patients with ACS are prescribed aspirin and prasugrel or aspirin and ticagrelor.

In the target trials, the interventions would be assigned during the hospital stay, as soon as patients are eligible for antiplatelet therapy. Our observational data set does not have information on medication given to patients at discharge, because HES does not include medications data. Therefore, the first time at which we have information on the antiplatelet regimen to which patients were assigned in hospital is when they receive their first primary care prescription/s for aspirin or DAPT, recorded in CPRD. It is reasonable to use these as a proxy for the medications that patients started in hospital, because patients’ general practitioners (GPs) are unlikely to change the prescriptions that were started in hospital.

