We will classify patients according to the first prescription recorded in CPRD during the first 2 months after hospitalisation for PCI, CABG or ACS. This 2-month window is based on variability in the amount of DAPT medication provided to patients in hospital following their PCI, CABG or ACS and hence variability in the time when they first request a repeat prescription from their general practice. A preliminary investigation showed that more than 75% of eligible patients have a prescription for one or more antiplatelet agents during this time period. If a patient only has a prescription for aspirin during the 2-month window after hospital discharge, they will be assigned to an aspirin only intervention. If patients also receive a prescription for clopidogrel, prasugrel or ticagrelor, they will be assigned to aspirin/clopidogrel, aspirin/prasugrel or aspirin/ticagrelor. If there is a prescription for more than one additional antiplatelet agent in the 2-month window, we will assign the patient to an intervention based on the agent prescribed first. For example, if a patient has an aspirin prescription and a prescription for clopidogrel before a prescription for ticagrelor, the patient will be assigned to the aspirin/clopidogrel intervention. Patients with no prescriptions in CPRD for aspirin, or aspirin and clopidogrel, prasugrel or ticagrelor within the 2-month window will be excluded from the main analysis. We will conduct sensitivity analyses of all eligible patients including those with unknown DAPT regimens or a major bleed prior to first DAPT prescription, by estimating assignment to DAPT interventions for those with no prescription data using multiple imputation based on a range of assumptions.^20^

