### Outcomes

The primary outcome will be any bleeding event, classified as type 2–5 by the Bleeding Academic Research Consortium (BARC) bleeding scale.^21^ For each patient, we will identify all bleeding events in HES and CPRD during follow-up. We will not be able to identify BARC type 1 bleeding events (bleeding that is not actionable and does not cause the patient to seek treatment) as type 1 assumes there is no interaction with the health system or healthcare professionals; therefore, no bleed event will be recorded in HES or CPRD. We have specified a comprehensive list of bleeding codes in CPRD and HES (see online supplementary appendix 1). These will be categorised according to anatomical site for descriptive purposes. Secondary outcomes will be: any major bleeding event (leading to hospital admission, inpatient HES); any minor bleeding event (recorded within CPRD data); all-cause mortality; cardiovascular mortality; mortality from bleeding (these will be identified from linked ONS data); MI; stroke; additional coronary intervention.

10.1136/bmjopen-2019-029388.supp1Supplementary file 1

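### In the conservatively managed ACS cohort, a PCI in a later admission can set the treatment arm and then count as an event in that arm

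*Protocol article*

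**What the plan says.** **Cohort.** For target trial 3, Table 1 lists "PCI or CABG performed at time of ACS diagnosis" as an exclusion. Study populations puts this into practice as ACS diagnosis codes "with no OPCS code for PCI or CABG in the same hospital admission". It adds: "Figure 1 shows full details of the inclusion and exclusion criteria". The figure is not in the text available here. The written text gives no rule for a PCI or CABG after discharge and does not define an admission for patients moved between hospitals.

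**Arm.** Interventions says the study will "classify patients according to the first prescription recorded in CPRD during the first 2 months after hospitalisation". The detailed rules then act on the whole window. Aspirin only requires that no other agent is prescribed in the 2 months. "If patients also receive a prescription for clopidogrel, prasugrel or ticagrelor, they will be assigned to aspirin/clopidogrel", or to the matching pair for the other agents. If there are two second agents, the earlier one decides.

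**Time zero.** Under Follow-up, the clock for ACS starts on the first day of the hospital episode with the diagnosis. Statistical analyses censors bleed-free patients at 12 months and states no handling of an intervening procedure.

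**Outcomes.** The primary outcome is any bleed of BARC type 2 to 5 in either database. The secondary outcomes include "MI; stroke; additional coronary intervention".

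**Regimens after PCI.** "For PCI patients, the interventions of interest are aspirin and clopidogrel, aspirin and prasugrel and aspirin and ticagrelor". None of these is aspirin alone.

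**The concern.** Target trial 3 is meant to compare aspirin with aspirin/clopidogrel in patients managed without a procedure. Under the written rules, something that happens after time zero (a PCI in a new admission) can determine which arm the patient is counted in from time zero. Because the PCI regimens of interest are all dual therapy, such patients are sorted towards aspirin/clopidogrel and away from aspirin only.

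Two results are exposed. Bleeding caused by the procedure would be credited to clopidogrel in the primary comparison. For additional coronary intervention, cause and effect run backwards: the procedure leads to the arm and is then counted as that arm's event. The bleeding estimates also feed the cost-effectiveness models.

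**Working it through.** **1. One hypothetical patient under the written rules.** Admitted with MI, no procedure, discharged. The GP prescribes aspirin in week 1. Readmitted for PCI in week 2. The GP prescribes clopidogrel in week 4.

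| Question | Answer under the written rule |
|---|---|
| In the ACS cohort? | Yes: no PCI code in the ACS admission |
| Arm? | Aspirin/clopidogrel: a second agent appears in the window |
| Start of follow-up? | The ACS episode, before the PCI and before clopidogrel |
| Bleed at the PCI? | A primary event in the clopidogrel arm |
| The PCI itself? | A secondary event in the clopidogrel arm |

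If the opening sentence on the first prescription were applied strictly, this patient would stay in aspirin only. A patient whose first GP prescription comes after the PCI would still be misplaced.

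**2. Do the planned safeguards catch it?** Adjustment uses baseline confounders, and the procedure comes after baseline. The first sensitivity set covers patients with no prescription, and these patients have one. The second looks at medication changes before a bleed as a sign of undocumented minor bleeding, and excludes patients only if more than 10% change. The third restricts to low bleeding risk. None targets a procedure between time zero and arm assignment.

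**3. The plan's own figures.** From Sample size: 8148 aspirin patients at 5% and 3082 aspirin/clopidogrel patients at 9%.
- Events: 8148 × 0.05 + 3082 × 0.09 = 684.8, against the stated minimum of 680.
- Detectable HR = exp[(z₀.₉₇₅ + z_power) / √(D·p(1−p)(1−R²))], with D = 680 and p = 1/3.5. At 90%/80% power this gives 1.317/1.268, 1.389/1.329 and 1.476/1.400 for R² of 0, 0.3 and 0.5. Table 2 has 1.32/1.27, 1.39/1.33 and 1.48/1.40.

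The sample size reproduces. The issue is bias.

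**4. Possible size for bleeding (assumed inputs only).** Suppose clopidogrel has no effect and the risk without a procedure is 5%. A share f of the clopidogrel arm has an early procedure and bleeds at risk q; nobody in the aspirin arm does. Then HR = ln(1 − [(1−f)·0.05 + f·q]) / ln(0.95).

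| f | q = 9% | q = 12% | q = 15% |
|---|---|---|---|
| 5% | 1.04 | 1.07 | 1.10 |
| 10% | 1.08 | 1.14 | 1.21 |
| 20% | 1.17 | 1.29 | 1.42 |
| 30% | 1.25 | 1.44 | 1.63 |

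If 2% of the aspirin arm is affected as well, the range over the same grid is 1.02 to 1.56. The smallest HR the ACS comparison is sized to detect (1.27, unadjusted, 80% power) is reached only at shares of about 20% to 30% with the higher risks.

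Starting instead from the planning rates, HR = ln(0.91)/ln(0.95) = 1.84. If 5% to 20% of the clopidogrel arm bleeds at 1.5 to 2 times 9%, the arm's risk becomes 0.09225 to 0.108 and the HR 1.89 to 2.23.

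**5. Additional coronary intervention (assumed inputs only).** If this route alone affected 10% v 2%, HR = ln(0.90)/ln(0.98) = 5.2; for 5% v 2% it is 2.5. With an assumed 10% background of other interventions in both arms, the cumulative hazards add: (0.1054 + 0.1054)/(0.1054 + 0.0202) = 1.68 and (0.1054 + 0.0513)/(0.1054 + 0.0202) = 1.25.

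**6. Power if such patients are excluded.** Removing 5% to 30% of the 3082 leaves 2928 to 2157 patients and 671 to 602 events. With p recalculated from the remaining counts, the unadjusted detectable HR at 80% power is 1.28 to 1.32.

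**The case against.** The best defence is that the article refers to Figure 1 for the full criteria, and a rule on transfers, event order or precedence between cohorts could be there. That stands as a limit on the point.

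A reader might infer that every patient transferred for PCI is coded as conservatively managed. The document does not support this: it never says whether an admission is one provider's record or a linked stay. Only the readmission route follows directly from the text.

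A reader might also infer that Table 1 and Study populations contradict each other. They do not: looking within one admission is a reasonable way to code a procedure at the time of diagnosis. In an analysis by assigned treatment, a later procedure is properly a follow-up event. The fault is that the arm may be read off after it.

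Nor does clopidogrel after PCI prove that the PCI caused it. Interventions notes that guidelines recommend dual therapy for conservatively managed ACS too, so some of these patients were already on it and are correctly placed. Those first given prasugrel or ticagrelor do not enter the clopidogrel arm.

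An obvious remedy, ignoring procedures before the assigning prescription, has its own flaw. It discards genuine events after time zero and makes that interval event-free by construction. This objection holds, and the fix avoids that step. Finally, the article openly declares the GP prescription as a proxy. Its justification is that GPs rarely change hospital prescriptions, but here a second hospital stay changes the regimen.

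**Conclusion.** The point holds for readmission: under the written rules, a PCI in a new admission within 2 months, followed by a clopidogrel prescription, can place the patient in aspirin/clopidogrel from the ACS date and count as an event there. It holds for transfers only if an admission means a single provider's record. It is weaker for CABG, for which aspirin alone is one of the regimens compared.

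The size cannot be derived from the document, which gives no share of patients with an early later procedure; every HR in steps 4 and 5 of the working rests on assumed inputs. An HR of about 5 for additional coronary intervention is a tempting headline, but it ignores all other interventions over 12 months and concerns one secondary outcome. Because Figure 1 may contain a further rule and the size is unknown, this is something that should be fixed, not a defect shown to invalidate target trial 3.

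**What to change.** 1. Define the ACS admission as the continuous inpatient stay with transfers joined, so that a PCI or CABG anywhere in that stay removes the patient from the ACS cohort.
2. For a PCI or CABG after that stay but within the 2-month window, assign the ACS arm only from prescriptions dated before the procedure. Where there are none, treat the regimen as unknown and include the patient in the multiple-imputation sensitivity analysis already planned.
3. Report the number of such procedures by arm. Add a sensitivity analysis of bleeding and of additional coronary intervention that either excludes these patients or starts follow-up in both arms at a common landmark at the end of the window. Do not drop procedures before the prescription as outcomes in one arm.

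If Figure 1 or the data analysis plan already contains such rules, stating them in the text is enough.

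**Cost.** Programming on linked records already held, and a slightly smaller ACS cohort. Even removing 30% of the clopidogrel arm moves the unadjusted detectable HR at 80% power only from 1.27 to about 1.32. The landmark version loses early bleeds, which the protocol expects to be the majority, and excluding patients on a later procedure is itself selection after time zero. Both therefore belong in sensitivity analyses. Step 2 also makes inclusion in the main analysis depend on a later event for patients with no earlier prescription, which is why their number by arm should be reported, with those of unknown regimen shown separately.
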